#### Activity Assessments

During the first 6 weeks of the study, the participants wore an activity tracker [57] and completed a short questionnaire on their mobile phone every morning and evening. The activity tracker was worn on the wrist of the nondominant arm or on the ankle in cases where the profession of the participant did not allow this. The tracker recorded activity counts at a sampling rate of 1 Hz. The participants were instructed to wear the tracker continuously, night and day, except when taking a shower or swimming. The questionnaire in the morning contained questions on estimates of bedtime, wakeup time, actual sleep duration, and quality of sleep. Sleepiness was assessed using the Karolinska Sleepiness Scale [58]. The questions in the evening were adapted from the International Physical Activity Questionnaire [59,60] and referred to the time spent in walking, sitting, and high and moderate amount of physical activity on that day. Furthermore, the participants were asked to rate the pain intensity during the day on a slider scale.

For the entire study duration, sensor data of the phone were collected from participants who agreed to the collection of these data and had a mobile phone with an Android operating system. The data collection was dependent on the availability of sensors in the phone and included acceleration and speed readings of the GPS location. In addition, data on the use of the app that provided the questionnaires were recorded.

#### Baseline Data and Adherence

General demographic data such as age, gender, education, occupation, and data on the participants’ history of back pain were collected using the questionnaire at T1. Participants' height and weight were measured using a personal scale and a bar before the first balance assessment. Completed exercises including timestamps were exported from the Valedo app and will be used to quantify adherence to the intervention. For patients in ET, data routinely assessed by physiotherapists at initiation of treatment, such as information on the diagnosis and dates of ET and physiotherapy appointments, were recorded.

#### Harms

The study was deemed low risk, as the Valedo home is a certified medical device and exercising is well established as a treatment for LBP. At the assessment visits, the participants were asked how they felt, and adverse events were documented on REDCap [31].

### Recruitment

ET patients were recruited at UHZ. Potentially eligible patients were contacted in person by the study personnel or physiotherapists, or they responded to flyers. The study personnel approached the patients at the initial appointments to keep the amount of therapy the patients had already received when entering the study similar. Participants without therapy for LBP were recruited by advertising on digital channels, word of mouth, and flyers. Participants received initial information on the study before the first assessment visit on the phone, either via email or in person. Reasons for dropping out were documented when specified by participants, and dropouts were not replaced. Email reminders were sent before assessment visits.

### Sample Size

Power was estimated using Gpower [61] using the *Linear multiple regression: Fixed model, single regression coefficient* menu. As this is a pilot study and we did not have data available to estimate the effect, we planned with an effect size of f^2^=0.063 and three predictors in the model to account for both factors and the interaction effect. The primary hypotheses refer to the effect of the EPF assignment on postural balance and the interaction effect of EPF with treatment status (patients in ET or no treatment); therefore, α was set to .025. To detect this effect at a power of 0.6, it would be necessary to include 80 participants. The number of patients receiving ET training at the UHZ is limited, whereas recruitment of more participants with LBP but not in therapy seemed feasible. Owing to these limitations, we planned to include 40 patients and 80 participants without therapy to account for dropouts.

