## Introduction

### Background

Digitalization is transforming health care and has the potential to increase the effectiveness of interventions. Novel tools can complement traditional therapies, offer new training formats, and allow different settings for providing interventions. As the number of those affected by low back pain (LBP) exceeds 500 million people worldwide [1] and self-management is recommended [2], digital tools may have a beneficial impact in reducing the total burden. It has been suggested that changes in spinal motor control can contribute to LBP persistence [3-5]. Digital tools that quantify trunk movements and provide feedback during physical exercises may be efficient in supporting people with LBP to improve their motor control of the trunk. As studies have demonstrated that fatigue of the trunk muscles [6] and trunk stiffness [7-9] affect postural balance, we hypothesize that exercising with postural feedback (EPF) on trunk movements can improve postural balance in people with LBP. Exergaming has shown promising effects in initial applications for musculoskeletal conditions [10]. However, available studies cover different conditions and interventions, and because of this heterogeneity, the results could not be numerically integrated in a recent review [10]. It was concluded that this field should be further explored [10]. In a review, it was shown that exercise interventions supported by digital tools for people with chronic LBP were successful only when provided in conjunction with other treatments and tested against the unaccompanied other treatment but not when compared by itself against another condition [11]. Similarly, improvements in postural balance may depend on being combined with parallel rehabilitative interventions. Therefore, this study included patients who received regular prescribed therapies, including exercise therapy (ET), and a group of participants who did not receive therapy for LBP.

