### Objectives

The primary research objective is to investigate whether a home exercise program with feedback on trunk movements can improve postural balance and other health-related outcomes in people with LBP. Secondary research objectives refer to the adherence to EPF, subgrouping participants with LBP based on digitally acquired data, comparison of objectively monitored activity data with self-reported activity data, and the relationship between fear of movement and postural balance. To keep the protocol concise, only the primary research objective is described in detail in this paper, and additional research questions will be addressed in future publications.

The hypotheses corresponding to the first research objective and the primary outcome of postural balance are as follows: EPF improves *postural balance*, and the improvements in *postural balance* because of EPF among participants not receiving therapy are more beneficial than the improvements in postural balance in ET patients receiving ET. Secondary outcomes include indicators for *motor control*, *pain intensity*, *disability*, *quality of life*, and *fear of movement*.

The intervention group is compared with a control group that did not receive an additional intervention. Potential difficulties in recording and comparing adherence in equal quality in groups with and without a digital tool played a role in this decision.

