### Study Design

The study was conducted at the Physiotherapy Occupational Therapy Research Department at the University Hospital Zurich (UHZ). The Cantonal Ethics Committee Zurich (Business Administration System for Ethics Committees 2018-02132) approved this study.

The study is a 2×2 factorial randomized controlled superiority trial, and it has been summarized in Figure 1. We aimed to recruit 40 patients with chronic, nonspecific LBP receiving ET training at the UHZ and 80 additional participants currently not receiving any treatment for LBP. Patients in ET continued with their regular prescribed therapies during the study participation, whereas participants without therapy for LBP were requested not to seek treatment for LBP while participating. At the second appointment (T2) at 3 weeks from inclusion, the patients and the participants without treatment for LBP were randomized to either receive or not receive the EPF intervention. This setup resulted in 4 groups: ET+EPF, ET, EPF, and no intervention. Study participants who did not receive EPF during the study (the ET alone and no intervention groups) had the possibility for EPF for 3 weeks after the completion of their last assessment (T4). Assessments of primary and secondary outcomes at the UHZ took place at inclusion (T1), 3 weeks after randomization (T2), after completion of the 3-week intervention period (T3), and after a second intervention period of 6 weeks without a predefined exercise schedule (T4).

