### Statistical Methods

We will test the primary hypotheses using multiple regression models (with the two factors patient or participant and EPF or no EPF and their interaction term as predictors, and T3−T2 differences as outcome) or nonparametric equivalent tests where required. We will use intention-to-treat analysis to examine intervention effects and replace missing values at T3 if less than 10% (12/120) of the data are missing. The method of replacing missing data has not been defined in advance. We will explore other assessment visits between T1 and T4 using multilevel models. Analyses related to other questions not described in this manuscript are not listed.

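### The stated 60% power with 80 participants at α = .025 holds only for one-sided tests, which the article never declares; two-sided tests at .025 give about 49% and need 102

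*Protocol article*

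**What the plan says.** The Sample Size section gives a complete power statement. The G*Power procedure is "Linear multiple regression: Fixed model, single regression coefficient". The inputs are given as "we planned with an effect size of f^2^=0.063 and three predictors in the model to account for both factors and the interaction effect". Because the primary hypotheses concern both the effect of exercising with postural feedback (EPF) and its interaction with treatment status, the section continues "therefore, α was set to .025". The result is "To detect this effect at a power of 0.6, it would be necessary to include 80 participants". Planned enrolment is then set at 40 patients plus 80 untreated participants, 120 in all, to allow for dropout. No dropout rate is given.

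The number of tails is not given there or elsewhere. Study Design says only "The study is a 2×2 factorial randomized controlled superiority trial". Statistical Methods says "We will test the primary hypotheses using multiple regression models", with the T3 minus T2 difference as outcome, and names no one-sided test. The hypotheses under Objectives are worded directionally: EPF improves balance, and the gains "because of EPF among participants not receiving therapy are more beneficial than the improvements in postural balance in ET patients".

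**The concern.** Lowering α from .05 to .025 because there are two hypotheses reads as a multiplicity adjustment of the usual 5% level. A reader who takes the regression coefficients to be tested two-sided, as standard regression output does, will take 60% as the power of a two-sided .025 test. It is not. The figure is the one that an unadjusted two-sided .05 test would give.

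Two things depend on this. First, the article's only power figure is right or wrong according to a setting that it does not report. Second, the significance threshold for the EPF effect is left open. The Results section says that analysis is ongoing, so the choice of tails could still be made, or appear to have been made, after the data were seen.

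**Working it through.** **Inputs, all from Sample Size:** f² = 0.063; three predictors; α = .025 per test; power 0.6; N = 80.

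**Formula.** For one coefficient in a fixed-effects regression with three predictors, the test statistic follows a noncentral t distribution with df = N − 3 − 1 = N − 4 and noncentrality δ = √(f² × N).

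**At N = 80:** df = 76 and δ = √(0.063 × 80) = √5.04 = 2.245.

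**Reproducing the stated figure.**
- One-sided α = .025: critical value t(.975; 76) = 1.992. Power = P(T > 1.992 | δ = 2.245) = 0.601. At N = 79 the power is 0.596, so 80 is the smallest N that reaches 0.60. This is the article's figure exactly.

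**Alternatives with the same f² and number of predictors.**

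| Test | Power at N = 80 | Smallest N for 0.60 | Power at N = 120 |
|---|---|---|---|
| One-sided .025 | 0.601 | 80 | 0.778 |
| Two-sided .05 | 0.601 | 80 | 0.778 |
| Two-sided .025 | 0.487 | 102 | 0.684 |

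For two-sided .025 the critical value at N = 80 is t(.9875; 76) = 2.287. Power is 0.598 at N = 101 and 0.603 at N = 102. The increase is (102 − 80)/80 = 27.5%, about 28%.

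**Could rounding or model size explain 80?** No. For f² from 0.0625 to 0.0635, two-sided .025 needs 101 to 103. With one to five predictors it needs 102 throughout.

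**Family-wise level.** Two one-sided tests at .025 sum to .025 + .025 = .05 one-sided (0.0494 if independent, 1 − 0.975²). Each has the upper critical value of a two-sided .05 test. Two unsplit two-sided .05 tests would sum to .05 + .05 = .10. The split therefore holds 5% one-sided and does not hold 5% two-sided.

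**Planned enrolment.** 120 × 0.85 = 102, so the planned 120 meets the two-sided requirement with up to 15% dropout. With none, two-sided power is 68%.

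**The case against.** The strongest reply is that nothing was miscalculated. The figure reproduces to the participant with one-sided tests, both hypotheses are directional, and the trial is called a superiority trial. Dividing .05 between two one-sided tests is a valid Bonferroni correction for directional hypotheses. Two-sided testing is a convention that the article never claims to follow. The article also condenses a longer protocol, which may state the tails. This stands in part. A reader might infer an arithmetic error, and the document does not support that. But the article prints the test, effect size, α, power and N together, and that statement cannot be read correctly without the missing element. Directional wording of a hypothesis does not declare a one-sided test.

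A reader might also infer that the trial was planned too small. It was not on this account: 120 exceeds 102.

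A third inference concerns the interaction. The Background suggests that "improvements in postural balance may depend on being combined with parallel rehabilitative interventions", whereas the hypothesis under Objectives puts the larger benefit in untreated participants. A one-sided test in the hypothesised direction would have almost no chance (below 0.01% at N = 80) of detecting an effect of equal size the other way. That is true of any one-sided test and presupposes an analysis that the article does not declare. The Background remark is also tentative. The point is secondary, because the Discussion states that the comparison between patients and untreated people will not be possible.

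Finally, recruitment closed with 3 patients and 32 untreated participants eligible, so no power figure can now change enrolment. That stands, and it lowers the weight of the point.

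**Conclusion.** The point holds as an undeclared test direction on which a stated power figure depends. At α = .025, 60% power with 80 participants is true one-sided; two-sided it is 49%, a shortfall of about 11 percentage points (0.601 − 0.487 = 0.114), and 60% needs 102 analysed participants. As calculated, the split controls family-wise error at 5% one-sided only.

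This rests on the article's own f², which it says had no data behind it, and on the noncentral t calculation for a single coefficient. That a one-sided setting was used in the software is an inference from the match, not a statement in the article.

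Severity is moderate. The planned 120 was adequate for the two-sided test, recruitment has ended at 35, and the interaction can no longer be usefully tested. What remains is a correct design record and a fixed threshold for the EPF effect.

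**What to change.** Preferred: in Sample Size and Statistical Methods, declare both primary tests two-sided at α = .025, and restate the planning figure as: 80 participants give 49% power; 102 are needed for 60%. It can be added that the planned 120 allowed for up to 15% dropout from that requirement.

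Alternative, if one-sided tests were intended: say so before the primary tests are run, state which direction of change in anterior-posterior sway counts as benefit, and state that the family-wise level is 5% one-sided. The figure of 80 for 60% power can then stand.

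If the full protocol or analysis plan already fixes the tails, cite it and align the article with it. The cost is wording only. Under the preferred option the stated power becomes less favourable and the threshold for the EPF effect becomes stricter.

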### Statistical Methods

We will test the primary hypotheses using multiple regression models (with the two factors patient or participant and EPF or no EPF and their interaction term as predictors, and T3−T2 differences as outcome) or nonparametric equivalent tests where required. We will use intention-to-treat analysis to examine intervention effects and replace missing values at T3 if less than 10% (12/120) of the data are missing. The method of replacing missing data has not been defined in advance. We will explore other assessment visits between T1 and T4 using multilevel models. Analyses related to other questions not described in this manuscript are not listed.

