## Results

The first participant was recruited in May 2019. Owing to the COVID-19 pandemic, the trial was paused from March to May 2020. In October 2020, data collection was concluded, with 38 participants providing informed consent. Of those participants, 3 patients and 32 participants passed the formal eligibility check and completed T1. The trial ended with the time that had been allocated for the study conduction, not based on interim analyses. Data analysis is ongoing.

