## Discussion

### Principal Findings

This study will provide information on how a digital intervention with feedback from IMUs on trunk movements affects postural balance and other outcomes in people with LBP. Daily questionnaires and continuous activity tracking will enable us to explore the development of pain intensity and other physical activities of each participant during the study in detail. The second intervention period without a predefined exercise schedule will give hints to the transferability of the results to a less controlled setting.

Within the allotted time, fewer participants could be recruited than initially planned, and only a few patients in ET could be recruited. Therefore, it will not be possible to compare the effects of the intervention between patients in ET and people with LBP who are not in treatment. Furthermore, when interpreting the results, it should be considered that no sham intervention was provided to the participants without therapy. Thus, general treatment-related factors are different among these groups.

The use of movement feedback from wearable sensors in exercise interventions is a promising approach to improve interventions. The detailed properties of the feedback given are likely to have an impact on the success of an intervention [22,23]. Continuous feedback received during a task performance is generally seen as disadvantageous for learning [22,23]. Conversely, feedback that shifts the focus outside of the body, for example, to a consequence or external visual representation of the movement, as used in this study, presumably enhances learning, even when provided very frequently [22]. However, it is not yet clear how interventions with feedback should best be designed for people with LBP [23].

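### The primary model and the split α still carry the EPF × treatment-status interaction, which the article says cannot be examined with at most 3 ET patients, so the EPF contrast to be tested is left undetermined

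*Protocol article*

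**What the plan says.** Objectives gives two directional hypotheses for the primary outcome: "EPF improves *postural balance*, and the improvements in *postural balance* because of EPF among participants not receiving therapy are more beneficial" than in ET patients. Sample Size repeats the pair as the EPF effect and "the interaction effect of EPF with treatment status (patients in ET or no treatment); therefore, α was set to .025". The power calculation follows suit: "we planned with an effect size of f^2^=0.063 and three predictors in the model to account for both factors and the interaction effect".

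Statistical Methods is worded in the future tense: "We will test the primary hypotheses using multiple regression models". The outcome is the change in sway from T2 to T3, and the model is specified in these terms: "with the two factors patient or participant and EPF or no EPF and their interaction term as predictors". That section gives no α and no coding of the factors.

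Results reports that "3 patients and 32 participants passed the formal eligibility check and completed T1", against 40 and 80 planned, and that analysis is still under way. On the contrast between ET patients and the untreated, Principal Findings in the Discussion then says "it will not be possible to compare the effects of the intervention between patients in ET and people with LBP", and the Abstract's Conclusions say the same. The Amendment section lists changes to eligibility, to access to EPF after the study and to the fear-of-movement questions. None of them touches the analysis.

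**The concern.** One of two primary hypotheses is both scheduled for testing and declared unanswerable in the same article. The surviving question, whether EPF improves balance, is affected as well. In a model with an interaction, the coefficient labelled EPF is the effect in whichever group is coded as reference or, under sum coding, an unweighted mean in which up to 3 ET patients count as much as 32 untreated participants. The text does not say which of these is the primary result. The choice could therefore fall to a software default, or be made after the estimates have been seen. It is also unclear what becomes of the share of α reserved for the interaction.

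**Working it through.** **The plan's own figure.** Inputs from Sample Size: f² = 0.063, three predictors, α = .025, power 0.6, N = 80. The test of a single regression coefficient has df = N − 3 − 1 and noncentrality √(f²·N). At N = 80, df = 76 and the noncentrality is √(0.063 × 80) = 2.245.

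- One-sided α = .025: power 0.601, and 80 is the smallest N that reaches 0.6. This reproduces.
- Two-sided α = .025: power 0.487, and N = 102 is needed. This does not reproduce.

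The document does not state sidedness. One-sided .025 has the same critical value in the direction of benefit as two-sided .05.

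**Layout assumed for the achieved sample.** The 35 are those who completed T1. Randomization took place at T2, and the numbers randomized, split by arm or analysed at T3 are not given. Three is therefore an upper bound for ET patients. I take all 35 as analysed, the 32 split 16/16, the 3 split 2:1, and residual SD = 1.

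**Interaction.** Its variance is the sum of 1/n over the four cells.

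- Planned (20/20/40/40): 1/20 + 1/20 + 1/40 + 1/40 = 0.150, SE 0.387.
- Achieved: 1/2 + 1/1 + 1/16 + 1/16 = 1.625, SE 1.275.
- Ratio: 1.275/0.387 = 3.3.

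The interaction implied by f² = 0.063 is √(0.063 × 120) × 0.387 = 1.06 SD in the planned layout, and about 1.00 SD in a balanced 80. Power to detect it in the achieved sample is 7–8% at two-sided .025 and 12–13% at two-sided .05.

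If all ET patients are in one arm, the design matrix has rank 3 of 4 and the interaction cannot be estimated. Randomization names height as the only stratification factor, so the text does not exclude this.

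**EPF coefficient.** SE in residual SD, and two-sided power for a true effect of 0.5 SD (an illustrative value):

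| Model and coding | What it estimates | SE | Power, α = .025 | Power, α = .05 |
|---|---|---|---|---|
| Interaction, untreated as reference | effect in the untreated | √(1/16 + 1/16) = 0.354 | 18.9% | 27.8% |
| Interaction, sum coding | unweighted mean of the two groups | √1.625 / 2 = 0.637 | 7.0% | 11.8% |
| Interaction, ET as reference | effect in ET patients | √(1/2 + 1/1) = 1.225 | 3.6% | 6.8% |
| Additive | precision-weighted mean | 1/√(8 + 2/3) = 0.340 | 20.4% | 29.8% |

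In the additive model the information is 1/(1/16 + 1/16) = 8 from the untreated and 1/(1/2 + 1/1) = 2/3 from ET patients. The untreated thus carry 8/8.667 = 92% of the weight.

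**The case against.** The article describes protocol version 3 of August 2019, so the interaction model is a fair record of what was prespecified, and the authors openly concede that the comparison failed. Factor coding is ordinary detail for an analysis plan that is not shown. With untreated participants as reference, keeping the interaction costs little: 18.9% against 20.4% power at two-sided .025. In a one-arm split, software that drops the aliased term leaves the additive model anyway.

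Most of this stands, and it limits the point. It does not remove it: the article already reports final enrolment, still words the model as the analysis to come, and never says which EPF contrast is left as primary.

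A reader might infer more than the documents support:

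- **A collapse in power from about 30% to 7%.** That sets sum coding at two-sided .025 against the additive model at two-sided .05, changing coding and α together. No section specifies sum coding.
- **That releasing α buys power.** N = 80 matches only one-sided .025. If that was the plan, a single test at two-sided .05 gains nothing: additive power is 29.7% against 29.8%.
- **A 25% chance that all three ET patients share an arm.** That is 2 × (1/2)³, which treats allocations as independent. Blocks of 2 and 4 were used, so the figure cannot be relied on.
- **That a change can still be made before unblinding.** Only outcome assessors were blinded, and analysis is described as ongoing.

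**Conclusion.** The inconsistency is real. A primary hypothesis, its model term and its share of α remain in the plan although the article says the question cannot be answered. Followed as written, the analysis gives an interaction with SE about 1.27 residual SD, or none at all, and an EPF coefficient whose meaning and SE (0.354, 0.637 or 1.225, against 0.340 additive) depend on a coding that the article does not fix. The main defect is the undetermined primary estimand. Under the most natural coding the loss of power is about 2 percentage points, and no choice of model or α rescues power at this sample size. The figures assume that all 35 are analysed with 16/16 and 2:1 splits. With fewer than two ET patients randomized, the interaction cannot be estimated at all.

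**What to change.** Make a dated change before the effect analysis, or label it post hoc if that analysis has begun:

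1. Withdraw the interaction as a primary hypothesis and drop it from the primary model.
2. Name the EPF effect as the single primary test, either in the additive model with treatment status as a covariate or in untreated participants only, with the other as sensitivity analysis.
3. Report the ET patients descriptively and limit the conclusion to people with LBP not in therapy.
4. State α together with its sidedness, without claiming a power gain from releasing the split.

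Adjusting for T2 sway and for height, the stratification factor, is a separate and optional improvement. The SEs above are not for that model.

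The cost is a short dated paragraph and the loss of a formal interaction test that the authors already concede. If effects have already been examined, there is the further cost of presenting the revised primary analysis as post hoc.

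### The missing-data rule replaces T3 values only below 10% missing and names no method and no fallback, so at 10% or more the primary T3−T2 regression is completers-only despite the intention-to-treat label

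*Protocol article*

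**What the plan says.** Three statements in the Statistical Methods section of the protocol article bear on this.

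- The analysis set: "We will use intention-to-treat analysis to examine intervention effects".
- The handling of missing T3 values, in the same sentence: the authors will "replace missing values at T3 if less than 10% (12/120) of the data are missing". The next sentence adds: "The method of replacing missing data has not been defined in advance". Nothing is said about 10% or more.
- The primary model: a multiple regression on patient/participant status, EPF assignment and "their interaction term as predictors, and T3−T2 differences as outcome". Multilevel models appear only as exploration: "We will explore other assessment visits between T1 and T4 using multilevel models".

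The Sample Size section gives the requirement, "To detect this effect at a power of 0.6, it would be necessary to include 80 participants", and the target, "we planned to include 40 patients and 80 participants without therapy to account for dropouts". The Recruitment section says that dropouts were not replaced. The Randomization section places randomisation at the T2 visit. The Results section reports that "3 patients and 32 participants passed the formal eligibility check and completed T1", and that data collection has ended and analysis is under way.

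**The concern.** A change score cannot be computed without T3. If T3 is not replaced, the participant drops out of the primary regression. The rule therefore keeps every randomised participant when few values are missing, where the choice of method matters little, and is silent when many are missing, where it matters most. An analyst who follows the text at 10% or more ends with a completers-only analysis under an intention-to-treat label.

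Two things are at stake. First, a completer comparison of change scores is biased if loss depends on T2 sway and differs by arm. Differential loss is plausible, since only the EPF arm is asked to complete nine home sessions between T2 and T3. Second, the replacement method will be chosen after data collection, in a trial of at most 35 randomised participants, where a few imputed values can move the estimate.

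**Working it through.** **1. The plan's own sample size.** Inputs from Sample Size: f² = 0.063, three predictors, α = 0.025, power 0.6. For a single regression coefficient, df = N − 4 and the noncentrality is √(0.063·N). With one-sided α = 0.025, N = 80 gives power 0.601, so the stated 80 reproduces. With two-sided α = 0.025, power at 80 is 0.487 and N = 102 would be needed. The document does not state sidedness; that is a separate matter and nothing below depends on it.

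**2. The margin against the cut-off.** Target 40 + 80 = 120; requirement 80. Implied allowance: (120 − 80)/120 = 33.3%, or 40 people. The rule needs fewer than 12 of 120 missing, that is at most 11 (9.2%).

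**3. Chance that replacement is switched off.** Binomial probabilities, assuming independent losses at a common rate:

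| T3 missing rate | P(12 or more of 120) | P(4 or more of 35) |
|---|---|---|
| 5% | 1.7% | 9.6% |
| 10% | 54% | 47% |
| 15% | 96% | 79% |
| 20% | 99.9% | 94% |

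**4. Losses before randomisation.** Losses between T1 and T2 come before randomisation and do not breach intention-to-treat. If all 40 allowed losses occurred, the count after T2 would stay below 12 only if at least 29 came before T2 (40 − 29 = 11). Taking the 10% of those randomised instead, at least 32 would have to come before T2: 8/88 = 9.1%, whereas 31 leaves 9/89 = 10.1%. The document gives no split.

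**5. Actual enrolment.** 3 + 32 = 35 completed T1, so at most 35 were randomised. 3/35 = 8.6% and 4/35 = 11.4%, so the fourth missing value passes the limit. Twelve missing would be 12/35 = 34%. For 4 to 11 missing, the percentage and the count in parentheses give different answers.

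**6. Size of a possible bias (illustration only).** Assumptions, none from the document: no true effect; T2–T3 correlation r of 0.5 to 0.7; dropout in the EPF arm only, with log-odds rising by 1 per SD of T2 sway. Control completers then have mean T2 = 0, and the spurious change-score contrast is −(1 − r) × (mean T2 of EPF completers, in SD).

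| EPF-arm dropout | Mean T2, EPF completers | Bias, r = 0.5 | Bias, r = 0.7 |
|---|---|---|---|
| 20% | −0.173 SD | 0.087 SD | 0.052 SD |
| 33% | −0.279 SD | 0.140 SD | 0.084 SD |

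With 1:1 allocation these are about 10% and 17% of the whole trial. The sign follows the assumption: if participants with more sway leave, EPF looks worse; if those with less sway leave, it looks better. If the control arm loses half as many with the same dependence on T2, the bias falls to about 0.02 to 0.07 SD. With equal rates it is zero. Adjusting for T2 leaves 0.003 SD or less in simulation.

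**7. Against sampling error.** With 17.5 per arm and the EPF dropout above, the change score has SD √(2(1 − r)), and the standard error of the contrast is about 0.28 to 0.38 SD. The bias is therefore roughly 0.2 to 0.4 of one standard error.

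**The case against.** The strongest objection concerns what the plan expected. A reader might infer that the authors planned for 33% attrition and so knew that the intention-to-treat analysis would not be done. The document does not support that. It states no dropout rate. The 120 target is also explained by the limited supply of ET patients and easier recruitment of untreated people, and part of any loss may precede T2. The 33% is an upper reading of the margin. What stands is that a T3 missing rate near 10% already makes replacement a coin toss.

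A reader might also take the 0.05 to 0.14 SD as the cost of the threshold. It is not. It comes from an unadjusted change score under assumed dropout in one arm, and adjusting completers for T2 would remove it. Deleting the threshold without conditioning on T2 would not be enough.

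Three further points have weight. A cap on imputation can be defended when much is missing, but then the plan must say what happens beyond the cap, and this one does not. The 12/120 can be read as a mere illustration of the percentage, in which case the percentage governs; even so, the count no longer fits, and the number randomised at T2 is not reported. Finally, the article condenses a longer protocol. That could excuse a missing fallback, but not the method, which the authors themselves say was left undefined in advance.

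**Conclusion.** The point holds as a conflict between a stated rule and a stated analysis principle. With T3 missing in 10% or more, the primary regression as written excludes randomised participants, and the text supplies neither a fallback nor a method. The conclusion that it becomes completers-only follows from the change-score outcome; those words are not in the text. The likelihood of crossing the limit is substantial: about even at 10% missing and 96% at 15% for 120 participants, with the limit passed at the fourth missing value if 35 were randomised.

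The consequence for the estimate is uncertain and probably modest. It rests on assumed dropout by arm, its relation to T2 sway and the T2–T3 correlation, none of which the document gives. In a pilot planned at power 0.6 that ended well short of its target, this is SHOULD-FIX.

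**What to change.** Delete the 10% (12/120) threshold and name one primary method that covers all randomised participants at any level of missingness:

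- a likelihood-based mixed model that conditions on T2. Entering T2 as a response with arm means set equal at that visit also keeps participants who have T2 only; or
- multiple imputation by arm from T1, T2, height and T4.

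Both assume that missingness depends only on observed data, which the report should say. Keep the patient/participant factor in the model. State that the EPF-by-status interaction, one of the two primary hypotheses, cannot be estimated in practice: three patients split at best two to one, and the Discussion already concedes that this comparison will not be possible.

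A promise to fix the method before unblinding would not fit, because only outcome assessors were blinded and analysis has begun. Label the method as specified after data collection, report the planned T3−T2 regression as a sensitivity analysis, and give the numbers randomised and missing at T3 by arm.

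The cost is a short revision of the Statistical Methods text, a little more analysis work and the post hoc label. No new data are needed: T1, T2 and T4 are scheduled assessments, and multilevel models of the visits are already foreseen.
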